## Methods

### Study design

For this study, a multicentre, prospective, randomized controlled trial will be conducted to compare the effects of A&AA with those of NRT, on smoking cessation. A total of 360 patients with severe nicotine dependence, who are willing to voluntarily quit smoking, will be randomly divided into a treatment group (A&AA) or a control group (NRT). The First Affiliated Hospital of Guangzhou University of Chinese Medicine, the Hong Kong Pok Oi Hospital, and the Shenzhen Chinese Medicine Hospital will be responsible for patient recruitment, screening, interventions, and the follow-up of 280, 30, and 50 patients, respectively. All outcomes will be assessed at The First Affiliated Hospital of Guangzhou University of Chinese Medicine. Management of the randomization sequence, blinding, and data analyses, will be carried out at the Clinical Research and Data Center of Guangzhou University of Chinese Medicine. Ethical approval for this study was received from the First Affiliated Hospital of Guangzhou University of Chinese Medicine (No. ZYYECK [2019] 099), and this study will be conducted according to the Declaration of Helsinki, 7th revision (2013). Informed written consent will be obtained from all patients. The flow diagram for patient selection and methodology is shown in Figure 1. This protocol is reported in accordance with the Standard for Reporting Interventions in Clinical Trials of Acupuncture recommendations (STRICTA) (20).

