### Sample size

According to a previous randomized, controlled study of acupuncture for smoking cessation (15), we expect that the success rates for smoking cessation will be on average 44% in the NRT (control) group and 60% in the A&AA (treatment) group, using the abstinence rate for smoking cessation at week 24 (24-h carbon monoxide [CO] clearance rate of <10 parts per million) as the primary outcome. Using PASS 2008 software, the sample size required for each group was estimated to be 152 cases by two independent sample rate comparison methods.

Therefore, considering an expected loss of 15% during the follow-up period, we will recruit a total of 360 (≈304/0.85) volunteers for this study. Allocation into the two groups will be assigned in a 1:1 ratio, and each group size will be set at 180.

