### Randomization and allocation

Eligible patients will be randomly assigned to receive A&AA or NRT *via* a central randomization system (Clinical Research and Data Center, Guangzhou University of Chinese Medicine). Random numbers will be generated using the stratified block method by a designer from the Clinical Research and Data Center, not involved in the study. Because of the obvious differences between the two types of therapies, blinding of patients and healers will not be possible; therefore, only outcome evaluators will be blinded to the treatment allocation.

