### Outcome measures

#### Primary outcome

The abstinence rate for smoking cessation at week 24 (number of people who quit smoking/total number of people) will be considered the primary outcome. Patients with a 24-h CO clearance rate of <10/1,000,000 at the 24th week of therapy, will be considered to have successfully quit smoking.

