### Statistical analysis

Data management and statistical analyses for this study will be carried out blingdingly by an independent third party (Clinical Research and Data Center, Guangzhou University of Chinese Medicine). The statistical tests involved in this study will include unilateral and bilateral tests with a significance level of α = 0.05. Statistical analysis will be completed using IBM SPSS 27.0.

All Subjects who will be randomized to undergo at least one treatment comprised the Intention-To-Treat (ITT) population of the study. Subjects who will be randomized into groups and underwent at least one treatment constitute the Safety group of this study. The Per-Protocol analysis data set (PPS), which refers to the cases that comply with the study plan, with the following conditions: the primary variables are clear, no baseline variables are missing, completed all scheduled studies for the 8-week treatment period, and subjects who seriously violate the protocol will be excluded. The safety dataset will be analyzed for subjects who have received at least one treatment after randomization. General demographic, clinical characteristics, and other baseline data will be used to compare the balance between the two groups. Primary outcome measures will be analyzed using ITT population, secondary outcome measures and other outcomes will be analyzed using PPS population. The safety analysis will use the safety population.At each time point, descriptive analyses will be performed to show the two groups of different means (SD and 95% CI) and the rate of outcome change. If the data follow normal distribution, the independent sample *T*-test will be used for comparison. If not, the rank sum test is applied. In order to distinguish therapeutic effects from temporal effects, analysis will be performed using a repeated measurement design.

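### The named efficacy tests leave out baseline scores and randomisation strata, and fix no test or effect measure for the binary primary outcome; the precision at stake lies mainly in the scales

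*Protocol article*

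**What the plan says.** All references are to the protocol article.

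- **Primary outcome:** the definition reads "The abstinence rate for smoking cessation at week 24 (number of people who quit smoking/total number of people) will be considered the primary outcome". Each patient is therefore a success or a failure.
- **Sample size:** the expected rates are "on average 44% in the NRT (control) group and 60% in the A&AA (treatment) group", and "the sample size required for each group was estimated to be 152 cases by two independent sample rate comparison methods".
- **Randomization and allocation:** "Random numbers will be generated using the stratified block method". The stratification factors are not named. Under Study design the three hospitals are responsible for the "follow-up of 280, 30, and 50 patients, respectively".
- **Statistical analysis:** an independent-samples t-test is used if the data are normal. "If not, the rank sum test is applied". Then, to separate treatment effects from time effects, "analysis will be performed using a repeated measurement design". No model, outcome list or covariates are given for that analysis. Baseline data are mentioned only for comparing the balance of the groups.
- **Table 1:** FTND, AUTOS, HAM-A, SAS and PSQI are all recorded at week 0 and at six later visits.
- **Safety analysis:** chi-square or Fisher's exact test is named, but only for adverse-event incidence.

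**The concern.** Two things do not fit together.

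First, the design collects information that the stated comparisons do not use. Stratified allocation is normally carried into the analysis. The week-0 value of a scale is usually one of the better predictors of its later value. Comparing follow-up scores without it leaves the confidence interval wider than it need be.

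Second, the rule for choosing a test turns on whether the data are normal, a question that only makes sense for continuous measurements. The trial was sized on a difference between two proportions, but the analysis section does not say how those proportions will be compared or on what scale the effect will be reported. Choosing the test after looking at the distribution also leaves the scale analyses open until the data are in. With a repeated-measures analysis planned as well, nothing says which result leads.

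**Working it through.** **1. What the sizing assumed.** Inputs are p₁ = 0.44 and p₂ = 0.60 from the Sample size section. Power is not stated there, and 80% is assumed here. Sidedness is not assigned to outcomes either: "The statistical tests involved in this study will include unilateral and bilateral tests with a significance level of α = 0.05".

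The pooled-variance formula, two-sided 5%, without continuity correction, is

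n = [1.96 √(2 × 0.52 × 0.48) + 0.8416 √(0.44 × 0.56 + 0.60 × 0.40)]² / 0.16²
= (1.3848 + 0.5870)² / 0.0256 ≈ 151.9, so 152 per group.

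This reproduces the plan's figure. A one-sided test at 85% power with continuity correction also gives 152, so the exact settings cannot be recovered. Either way it is a two-proportion test. For the total, 304 / 0.85 = 357.6, which agrees with 360.

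**2. Would the named tests be invalid on 0/1 data?** Simulation with 152 per arm, 4,000 runs; power at 44% v 60%, type I error at 52% in both arms:

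| Test | Power | Type I error |
|---|---|---|
| t-test | 0.785 | 0.049 |
| Rank-sum | 0.784 | 0.049 |
| Chi-square | 0.785 | 0.049 |

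The p-value hardly depends on which is used. The difference is in what is reported: a rank-sum test by itself gives no risk difference, risk ratio or odds ratio.

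**3. What a named effect measure would look like.** At the planning rates with 152 per arm, SE = √(0.4864 / 152) = 0.0566. The risk difference is 16 points, with 95% CI 16 ± 1.96 × 5.66, or 4.9 to 27.1 points.

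**4. Stratifying the primary outcome by centre.** Centre is assumed to be the stratum, with 280, 30 and 50 patients and all 360 analysed. The two small centres are shifted by assumed amounts in opposite directions; 5,000 runs:

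| Centre shift | Power, unadjusted | Power, Cochran-Mantel-Haenszel |
|---|---|---|
| 0 | 0.864 | 0.864 |
| ±10 points | 0.865 | 0.865 |
| ±20 points | 0.874 | 0.876 |

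The gain is negligible. If baseline covariates explained an assumed 2% to 15% of the outcome variance, power at 152 per arm would rise from 0.80 to roughly 0.81 to 0.86.

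**5. Baseline adjustment of the scales.** Compared with an unadjusted comparison of follow-up scores, adjustment for the week-0 score multiplies the variance by 1 − r², where r is the baseline-to-follow-up correlation. The article gives no r, so the values are assumed:

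| r | 1 − r² | SE ratio √(1 − r²) | Equivalent sample 1/(1 − r²) |
|---|---|---|---|
| 0.3 | 0.91 | 0.95 | 1.10 |
| 0.5 | 0.75 | 0.87 | 1.33 |
| 0.6 | 0.64 | 0.80 | 1.56 |

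Secondary outcomes use the per-protocol set, which already requires complete baseline variables, so the adjustment loses no patients there.

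**The case against.** The strongest reply is that this is an article, and that model form, covariates and strata terms are usually left to an analysis plan that is not shown. A repeated-measures analysis is already planned and may include the week-0 value. This stands in part: if that analysis does use baseline, some of the gain in step 5 is already secured. But the article does more than stay silent. It names specific unadjusted tests, gives a data-driven rule for choosing between them, and does not say whether they or the repeated-measures analysis lead.

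Three stronger readings are tempting, and the document does not support them.

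- *The 0/1 primary outcome is sent to the rank-sum test.* The rule follows a sentence about means and SDs and is most naturally about continuous data. The fair reading is that no test is named for the binary outcome, not that a wrong one is prescribed.
- *The primary result will have no effect estimate.* That is too absolute. The section on missing data foresees point estimates and a pooled effect with 95% CIs, though only on some missing-data routes and without naming the measure. The cost-effectiveness section uses the primary outcome as its effectiveness index for an ICER, which requires a between-arm difference.
- *Five scales at six visits mean thirty separate tests.* The phrase about each time point introduces descriptive analyses. The article does not say that the tests are run at every visit.

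**Conclusion.** The point holds in a limited form. The stated efficacy comparisons are unadjusted and chosen by a normality check. Neither the strata nor the week-0 scores enter any efficacy analysis as described. The binary primary outcome has no named test or effect measure, although it was sized as a two-proportion comparison.

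A reader might infer that the primary test is invalid or loses appreciable power by ignoring centre. The checks show neither: error rates are close to nominal, and stratifying by centre changes power by at most 0.002 in the scenarios tried. For abstinence the issue is clarity about what will be estimated. For the scales it is precision: 9%, 25% or 36% less variance at r = 0.3, 0.5 or 0.6, measured against an unadjusted comparison of follow-up scores.

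These sizes rest on assumptions not in the article: 80% power, centre as the stratum, the centre shifts, the share of variance explained, and the correlations.

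**What to change.** - **Week-24 abstinence:** name the primary comparison as a risk difference with 95% CI, stratified by the factors used in the randomisation (for example Mantel-Haenszel), and state what those factors are.
- **Each scale:** make the repeated-measures analysis already planned the lead analysis. Specify it as a mixed model with baseline score, randomisation strata, visit, arm and arm-by-visit, and a prespecified week-24 contrast.
- **Test selection:** drop the normality-based choice between t-test and rank-sum test.

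The cost is a few sentences of analysis-plan wording and slightly more analysis work, with no new data. The Discussion reports that recruitment is under way, so the change should be recorded and dated before outcome data are examined by arm.

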### Safety analysis

Patients will be questioned about adverse events at each visit, and all adverse events will be recorded and assessed by investigators to identify any causal relationships with the treatment. Blood tests, urinalysis, and electrocardiographic examinations will be performed before and after treatment. Furthermore, Blood lipids, kidney and liver function tests will be re-examined at weeks 16 and 24, and all abnormal changes from the baseline laboratory tests will be evaluated by investigators. Patients will have to report any adverse events that occur at any time to the study team.

Safety will be evaluated by tabulations of adverse events and will be presented with descriptive statistics at baseline and at follow-up visits for each treatment group. All details about adverse events, such as timing, severity, treatment, and causality to the intervention, will be recorded in CRF tables and descriptive statisticswill be performed. Chi-square test or Fisher's exact probability will be used to compare the incidence of adverse events between the two groups, and rank sum test will be used to compare the severity of adverse events.

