Since 2015, complementary and alternative medicine for substance use disorders has increasingly gained attention, and acupuncture may be a hotspot in this field (13). Various types of acupuncture, such as hand acupuncture, ear acupuncture, laser acupuncture, have gained attention in many countries as therapeutic interventions for smoking cessation (14). In a smoking cessation trial in Norway (15), the experimental group received an acupuncture intervention at the “Shenmen,” “Mouth,” and “Liver” acupoints of the ear, as well as at the acupuncture points, Kongzui (LU 6) and Lieque (LU 7), leading to significant changes in the taste of cigarettes and the desire to smoke, compared with the control group. A multicentre, randomized trial of 300 patients in China (16) also showed that the effects of acupuncture on smoking cessation were not inferior to NRT. Available evidence supports the acupuncture therapy have very wide popularization and application prospects in smoking cessation, while it is also suggested that single type acupuncture therapy is relatively insufficient in the long term of the abstinence rate, and the evidence is insufficient in the efficacy of combined acupuncture therapy (17–19). Thus, we carry out this RCT to observe the effect of combined acupuncture therapy on smoking cessation.

This multicentre, randomized, controlled clinical trial, which is based on a previous study of acupuncture for smoking cessation, will be the first to evaluate whether the combination of a short-term but strong stimulation, elicited by acupuncture and the long-term, milder stimulation elicited by auricular acupressure, will lead to better smoking cessation outcomes. Additionally, we hope to determine whether this treatment (A&AA) has better smoking cessation outcomes and is safer than NRT. We also hope to evaluate the benefits of A&AA from the perspective of health economics, in order to develop effective and affordable smoking cessation plans.

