**Figure 3 F3:**
[figure not shown]
Nomenclature and location of auricular points (21).

The A&AA interventions will be performed simultaneously twice a week for a total treatment course of 8 weeks.

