The treatment group will receive A&AA treatment. We designed acupoint combination of acupuncture and ear acupuncture based on traditional acupuncture theory and previous literature studies (22, 25–28). Baihui and Yintang can connect the Du meridian to regulate the consciousness and calm the mind which are reported to reduce dependence, relieve anxiety for addicts (29). Lieque, a acupoint of lung meridian connected with Conception Vessel, can diffuse and regular the lung qi as well as nourish yin-fluid to relieve pharyngeal discomfort in smokers (30). Acupuncture at Hegu can regulate qi movement of spleen and stomach to relieve the discomfort caused by smoking cessation (31). Auricular acupuncture was incorporated into our treatment strategy with the aim of working with manual acupuncture to produce a longer treatment effect for patients to achieve a longer and more stable abstinence rate. Likewise, auricular acupoints play a role in tranquilizing the mind and regulating the Qi of lung and stomach. And it is reported that the continuous stimulation of auricular acupoints will produce the release of neurotransmitters and the change of endocrine that conducive to smoking cessation (32–34).

The limitations of this trial must be acknowledged. First, due to the long experimental and follow-up periods, a high dropout rate may occur, especially in the treatment group. Because of busy professional lives, job mobility, or the lack of acupuncture knowledge, patients may lack the motivation to complete a 24-week course. To reduce this dropout rate, the researchers will have to fully explain the process during the initial stage and will maintain positive contact with volunteers. Second, because this is an unblinded design, there is the possibility of bias due to the expectations or biases of the participants or research staff. To minimize this potential source of bias, researchers will provide public education about acupuncture for smoking cessation, including the principles of acupuncture, and will share stories of successful cases. Last but not least, we must acknowledge that this design lacks a professional psychologist to educated patients, although an educational video has been recorded and all operators have been trained.

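### Adverse-event incidence is compared crudely, with no stated window and no allowance for time observed, so unequal dropout or off-treatment events could distort the safety comparison with NRT

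*Protocol article*

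**What the plan says.** - **Aim.** The Background gives a comparative safety question: "we hope to determine whether this treatment (A&AA) has better smoking cessation outcomes and is safer than NRT". The Abstract attaches a safety assessment to the primary outcome, while the Secondary outcomes section lists safety there. No sample size is given for it.
- **Test.** Safety analysis: "Chi-square test or Fisher's exact probability will be used to compare the incidence of adverse events between the two groups". A rank sum test is added for severity.
- **Population.** Statistical analysis: everyone who received at least one treatment after randomization.
- **Collection.** "Patients will be questioned about adverse events at each visit". Table 1 ticks the adverse event record at weeks 2, 4, 6, 8, 16 and 24.
- **Treatment length.** A&AA is "performed simultaneously twice a week for a total treatment course of 8 weeks", and the NRT course is also 8 weeks. So 16 of the 24 weeks are off treatment.
- **Dropout.** Sample size allows 15% loss overall. The limitations in the Discussion add that "a high dropout rate may occur, especially in the treatment group". No rate by arm is given.
- **Description.** Summaries are given by arm: "Safety will be evaluated by tabulations of adverse events and will be presented with descriptive statistics at baseline and at follow-up visits for each treatment". The case report form holds more: "All details about adverse events, such as timing, severity, treatment, and causality to the intervention, will be recorded in CRF tables". The section Assessment of adverse events includes the date of onset.

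**The concern.** A chi-square or Fisher test on the share of patients with an event gives a patient seen for 4 weeks the same weight as one seen for 24. This is harmless when both arms are observed for similar times. Here the protocol itself names a possible imbalance: if more A&AA patients leave early, fewer of their events can be recorded, and the crude proportion moves towards the conclusion the trial hopes for.

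Separately, the test is not limited to the treatment period. If events from all 24 weeks enter the numerator, complaints unrelated to either treatment in weeks 8 to 24 are added to both arms and can hide a real on-treatment difference, whichever arm it favours.

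**Working it through.** **Inputs from the protocol.** 180 per arm, 8 weeks of treatment, events collected to week 24, 15% overall loss, α = 0.05. The only figure the plan derives is the abstinence sample size. For 44% v 60%, a pooled two-sided 5% test with 80% power (the power is inferred) gives 152 per arm, as stated, and 304/0.85 = 357.6, rounded up to 360. This does not bear on safety except by fixing 180.

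**Assumptions.** The documents give no adverse-event rate and no dropout by arm. I take true 24-week risk p of 10% to 40%, equal in both arms, and dropout of 20% on A&AA v 10% on NRT (mean 15%). The more extreme case is 25% v 5%, with the same mean. All 180 per arm are taken as treated. The protocol mentions both one- and two-sided tests without assigning them. I use two-sided 0.05, so the nominal chance of a false finding in favour of A&AA is 2.5%.

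**1. Bias from unequal dropout**

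With constant hazard h = −ln(1−p)/24 and dropout times uniform on 0 to L weeks, the chance that a dropout has a recorded event is q = 1 − (1 − e^(−hL))/(hL). Crude incidence in an arm with dropout d is (1−d)p + dq.

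Worked case: p = 40%, all dropout within 8 weeks (L = 8).
- h = 0.02128, hL = 0.1703, q = 1 − 0.1566/0.1703 = 8.05%.
- A&AA: 0.80 × 40 + 0.20 × 8.05 = 33.6%.
- NRT: 0.90 × 40 + 0.10 × 8.05 = 36.8%.
- Risk ratio 0.913, gap 3.2 points, standard error 5.03 points.
- Chance of falsely finding A&AA lower: Φ(3.19/5.03 − 1.96) = Φ(−1.33) = 9.2%.

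Ranges over p = 10% to 40%:

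| Dropout A&AA v NRT | Pattern | Crude risk ratio | False finding for A&AA |
|---|---|---|---|
| 15% v 15% | any | 1.00 | 2.5% |
| 20% v 10% | events on treatment only, dropout over 24 weeks | 0.983–0.985 | 2.8–3.3% |
| 20% v 10% | constant hazard, dropout over 24 weeks | 0.948–0.952 | 3.6–5.5% |
| 20% v 10% | constant hazard, all dropout in weeks 0–8 | 0.910–0.913 | 4.6–9.2% |
| 25% v 5% | events on treatment only, dropout over 24 weeks | 0.967–0.969 | 3.2–4.2% |
| 25% v 5% | constant hazard, all dropout in weeks 0–8 | 0.828–0.834 | 8.0–24.4% |

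**2. Dilution if all 24 weeks are counted**

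With 8-week risk a and background risk b in weeks 8 to 24, 24-week incidence is 1 − (1−a)(1−b). For 10% v 20% and b = 10%: 1 − 0.90 × 0.90 = 19% and 1 − 0.80 × 0.90 = 28%.

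| Background b | A&AA v NRT | Risk ratio | Power, 180 per arm |
|---|---|---|---|
| 0% | 10% v 20% | 0.50 | 76% |
| 10% | 19% v 28% | 0.68 | 52% |
| 20% | 28% v 36% | 0.78 | 37% |
| 30% | 37% v 44% | 0.84 | 27% |

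For 20% v 35% on treatment, the same backgrounds give power of 89%, 77%, 64% and 51%.

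**3. Does an 8-week window alone cure the bias?**

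Take p = 40% over 24 weeks, so 8-week risk is 1 − 0.60^(8/24) = 15.7%, with all dropout in weeks 0 to 8. At 20% v 10% the window records 14.1% v 14.9% (false finding about 4%). At 25% v 5% it records 13.8% v 15.3% (about 6%). These compare with 9.2% and 24.4% over 24 weeks. Most of the bias goes, but not all.

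**The case against.** The best reply is that a protocol article may leave the treatment-emergent window and exposure adjustment to an analysis plan that is not shown, and that chi-square or Fisher on patients with an event is a conventional comparison. That is fair, and the lack of a window would not be a point on its own. What remains is that the article chose the test and the population, stated a comparative safety aim and foresaw unequal dropout, and that this test is weak in exactly that situation.

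Other parts of the reply stand and limit the point:
- A reader might infer that A&AA will look safer. The Discussion says only that high dropout may occur, gives no rate by arm and plans to reduce it. A patient who leaves because of an event already reported is still counted, and contact with non-responders is planned.
- A reader might infer that the test pools all 24 weeks. The period is not stated. Timing and causality are recorded and results are shown by visit, so on-treatment events can be separated. These displays are descriptive, however, and the named incidence test uses none of them.
- A reader might take a false-finding rate near 24% as the expected size. It needs 25% v 5% dropout, all of it early, 40% risk and constant hazard to week 24. None of these is in the documents.
- A reader might infer that the plan as a whole leans towards A&AA. Dilution pulls towards no difference, so if NRT truly causes more events it works against the hoped-for conclusion. The net direction cannot be determined.

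**Conclusion.** The point holds as a cheap improvement of minor to moderate weight. The named between-arm test on adverse-event incidence ignores time observed and is not limited to the treatment period, although the protocol foresees dropout that may be higher on A&AA. At a plausible 20% v 10% dropout the distortion is modest: a crude risk ratio of about 0.91 to 0.985 when true risks are equal, and a false finding in favour of A&AA in about 3% to 9% of trials against 2.5%. It vanishes with equal dropout and is larger only under more extreme assumptions. Dilution ranges from none, if there are no off-treatment events or they are not counted, to a serious loss of power. The documents do not support saying that the safety result will be biased, only that the stated test does not guard against it. Safety is unpowered and sits with the secondary outcomes, which also keeps the weight down.

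**What to change.** In Safety analysis:

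1. Make the main between-arm comparison the patients with an adverse event that starts or worsens during the 8-week treatment period plus a short tail of stated length. Both arms attend twice weekly in those 8 weeks.
2. Accompany it with events per patient-week or time to first event, censored at last contact, for the treatment period and for the full 24 weeks. This is needed because the 8-week proportion still carries some bias from dropout before week 8. It assumes that leaving is unrelated to unrecorded events, so time observed and reasons for leaving should be shown by arm.

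The cost is analysis wording only, since onset dates are already recorded. The small downside is that late events move from the main test to the 24-week table, where they must still be reported in full.
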